### Sample size

Simulation studies by Teare et al. [71] indicate that small studies (less than 50 participants, 25 per group) do not provide realistic estimates of results, indicating that group sizes should be at least 25, and that preferably a minimum of 35 participants per group be employed where possible.

Although it did not specifically include the ABS, a recent systematic review [41] reported standardised mean differences (i.e. Cohen’s *d* or the difference in group means divided by the pooled group standard deviation) in 2-h and 24-h post-administration levels of agitation between intramuscular olanzapine and placebo ranging from 0.36 to 1.93. In regard to other populations, a study of agitation levels in patients with schizophrenia following administration of intramuscular olanzapine or placebo found a standardised mean difference of 1.27. The minimal clinically important difference for improvement in irritable/aggression scale scores in TBI [68] is equal to a standardised mean difference of 0.50, the conventional Cohen medium effect size, with a large Cohen effect size being defined as a standardised mean difference of 0.80. Given the above prior findings, a large effect size would be expected. Using the Stata 15 power and sample-size procedure, we calculated the required sample size to detect a standardised mean difference/effect size of 0.80 (e.g. 0.80 of the standard deviation of 4.1 for mean daily ABS score at outcome reported in the pilot study of McKay et al. [26], *n* = 125) with a statistical power of 0.80 and a 2-tailed alpha of 0.05. Results indicated a required sample size of 26 patients per group, for a total of 52 patients.

A sample size of 26 patients per group, or 52 in total, exceeds the lower threshold of 50 patients identified by Teare et al. [71] and is clinically practical. Assuming 10% attrition, 29 patients (26/(1–0.10) = 28.9, conservatively rounded to 29) per group would be required, for a total of 58 patients, in order to complete the study with 52 patients.

### Statistical methods

#### Analysis of primary and secondary endpoints

Descriptive statistics will be reported using frequencies and percentages for categorical data. Percentages will be calculated based upon the number of patients for whom data are available. Continuous or dimensional variables will be summarised using means and standard deviations, with medians and interquartile ranges (difference between 25th and 75th percentiles) reported for potentially skewed data such as SF-12 PCS and MCS scores.

For the analysis of the primary endpoint, difference in mean daily ABS scores during PTA between olanzapine and control groups, a mixed model/multilevel regression framework [72], taking into account duration of PTA, will be employed. Although a difference between group means corresponding to a large effect size (0.80 of the pooled group standard deviation) is expected, a clinically significant improvement is defined as a difference in group means of the mean daily ABS scores within PTA equal to at least half a pooled group standard deviation difference, the minimal clinically important difference for improvement in irritable/aggression scale scores in TBI [68]. In regard to secondary endpoints, regression methods appropriate to the type of outcome variable will be employed. Comparison of the two groups on dimensional secondary endpoints such as ABS at discharge and WPTAS scores will be analysed using linear regression or median quantile regression. Median quantile regression, based upon the median and so less affected by very high or very low scores, will be employed for possibly skewed variables, such as SF-12v2 MCS and PCS scores, that may not meet the assumptions of linear regression [73].

Secondary endpoints involving count data including number of days in PTA, number of clinically agitated days, length of stay in hospital, agitation scores on discharge, number of “treatment failures” and number of AEs and other measures of treatment safety will be analysed using regression models for count data (Poisson or negative binomial regression as appropriate; [74]).

All statistical tests will be two-tailed, with alpha or statistical significance level set to *p* < 0.05. 95% confidence intervals will be reported throughout. The number of missing observations will be reported. Analyses will assume intention to treat, with all patients analysed as randomised.

If imputation of missing data is required, the method of imputation will depend on the amount of missing data, its characteristics and whether it is the covariates and/or outcome variables that are missing [75]. Following suggested practice, complete case analysis will be reported along with imputation. Multiple imputation will be undertaken separately for each group, and a sensitivity analysis for the assumptions (i.e. missing completely at random) performed [75]. Full details of the imputation procedure will be reported [76]. Statistical analysis will be conducted by a professional Epworth HealthCare or Epworth HealthCare accredited biostatistician, blinded to group assignment, employing a standard statistical package such as Stata 15 or higher. A detailed Statistical Analysis Plan will be prepared by the biostatistician(s).

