### Inclusion criteria

(1) Currently under hospital care at Epworth HealthCare for TBI rehabilitation, (2) a history of blunt head trauma with a loss of consciousness and an initial Glasgow Coma Scale of 3–14 and/or a period of PTA, (3) judged to be in PTA (score < 12) on the Westmead Post Traumatic Amnesia Scale (WPTAS; [44, 45]), (4) judged to be in a state of clinically significant agitation (score > 21) on the Agitated Behaviour Scale, (5) aged 18 years or older, (6) provision of signed and dated Medical Treatment Decision Maker Participant Information and Consent Form by the participant’s Medical Treatment Decision Maker (MTDM; during PTA) and (7) provision of signed and dated Participant Information and Continuing Consent Form by the participant (upon PTA emergence).

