### Participant timeline

The participant timeline is displayed in Table 1 schedule of activities.

**Table 1 Tab1:** Schedule of activities

Study phase	Screening/consent	Baseline/randomisation	Treatment period (PTA)	Post-PTA	Discharge	Three-month follow-up
ACD/ MTDM identification	X					
Trial introduction	X					
MTDM consent	X					
Screening	X					
Participant consent				X		
Randomisation		X				
Demographics^a^		X		X		
Medical record^b^		X	X		X	
Medical information^c^		X	X	X		
Blood test(s)^d^		X	X	X		
WPTAS		X	X			
ABS		X	X	X	X	
Simpson-Angus Scale		X	X			
Administer treatment			X			
Treatment log			X			
AE monitoring^e^			X			
RAVLT				X		
SDMT				X		
SF-12				X	X	X
FIM				X	X	
MPAI-4						X
PDHSUQ						X

^a^Age, gender, years of education, marital status, pre-injury employment/study status, drug and alcohol history, psychiatric history

^b^One or more of date and cause of injury, Glasgow Coma Scale, PTA duration, imaging results, surgical intervention, other injuries, Injury Severity Score, therapy hours and number of sessions, special nursing care, medication details, number of patients on ward

^c^Weight, BP, HR, WC

^d^Assessing fasting lipids, fasting glucose, HBA1C, creatinine

^e^Respiratory issues, lethargy, nausea, vomiting, difficulty swallowing, constipation, urinary retention, dizziness, seizures

#### Baseline—day 0

Following eligibility confirmation and randomisation, the following information will be gathered from the participant’s medical record: baseline WPTAS and ABS, demographic information (age, gender, years of education, marital status, pre-injury employment/study status, drug and alcohol history and psychiatric history) and medical information (date and cause of injury, Glasgow Coma Scale score, PTA duration, imaging results, surgical intervention, other injuries, injury severity score, therapy hours, special nursing care and medication details). Pre-treatment measures of weight, blood pressure (BP), heart rate (HR) and waist circumference (WC) will be conducted by nursing staff. Blood tests assessing fasting lipids, fasting glucose, haemoglobin A1c (HBA1C) and creatinine will be conducted. The Simpson-Angus Scale (SAS; [49]) will be completed by the patient’s treating physiotherapist, in order to assess the presence of extrapyramidal symptoms.

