#### Treatment—day 0 until emergence from PTA (or 6 months maximum)

The treatment period will last from day of completion of baseline assessments until the patient is deemed to have emerged from PTA or until 6 months have elapsed. Emergence from PTA is defined as the first of three consecutive days on which a score of 12/12 on the WPTAS is achieved. Participants will be administered their randomised dose. They will also receive optimal environmental management as per guidelines [7]. WPTAS and ABS scores will be recorded by nursing staff or the patient’s clinical neuropsychologist. Need for dosage escalation and rescue medication use will be monitored by study staff. To describe concomitant care and inform health-economic evaluation, the number of patients on the ward, therapy hours and number of sessions and medication use including name and dose regimen will be recorded from the participant’s medical file.

AE monitoring will occur weekly. Clinically significant changes in these parameters will be recorded as AEs and a decision made by the treating doctor in consultation with a psychiatrist and the DSMC as to whether serious AEs necessitate withdrawal from the study.

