### Outcomes and measures

#### Primary outcome

To assess the efficacy of the atypical antipsychotic olanzapine in reducing agitation in patients in PTA following TBI over and above recommended environmental management, we will examine the difference between active and placebo groups’ mean daily score on the ABS during PTA. This outcome will include all daily ABS assessments throughout the treatment period. The ABS is a widely used measure of agitated behaviour in TBI [56–58]. Completion involves the observer rating the presence of 14 agitated behaviours based on the past 8-h period. Internal consistency is high, and construct validity and inter-rater reliability have been established [57–60]. Nurses and clinical neuropsychologists who complete the ABS at Epworth HealthCare are trained in its use.

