#### Secondary outcomes

To examine the safety of olanzapine administration in PTA patients: Difference between olanzapine and placebo groups’ mean number of AEs (as captured via trial bloodwork, Adverse Events Questionnaire, Simpson-Angus Scale, measures of weight, BP, HR, WC) during PTA.To determine whether olanzapine treatment reduces the number of clinically agitated days during PTA: Difference between olanzapine and placebo groups’ mean number of clinically agitated days (ABS score > 21) during PTA.To determine whether olanzapine treatment alters level of agitation at hospital discharge: Difference between olanzapine and placebo groups’ mean ABS score at discharge, controlling for ABS score at treatment commencement.To determine whether olanzapine treatment alters level of cognition in PTA: Difference between olanzapine and placebo groups’ mean levels of PTA as measured using the WPTAS [44, 45], controlling for WPTAS score at baseline. Mean scores will encompass daily assessments of the WPTAS throughout the treatment period, from first day of treatment until emergence from PTA (defined as the first of three consecutive days on which a score of 12 on the WPTAS is obtained). The WPTAS is commonly used in Australia to assess PTA. Seven items on the WPTAS assess orientation to time, person and place, and five assess anterograde memory (therapist face, name and three picture cards). Good construct validity and inter-rater reliability have been demonstrated [45, 61]. Nurses and clinical neuropsychologists who administer the WPTAS at Epworth HealthCare are trained in its use.To determine whether olanzapine treatment alters PTA duration: Difference between olanzapine and placebo groups’ mean number of days in PTA (from date of injury until emergence from PTA based on three consecutive scores of 12 on the WPTAS).To determine whether olanzapine treatment alters cognitive performance following PTA emergence:

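### The primary model of daily ABS names no adjustment for baseline ABS, although that score is collected and baseline values are controlled for in two secondary outcomes; the cost is efficiency, not bias

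*Protocol article*

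**What the plan says.** **Primary endpoint.** Under Primary outcome, the protocol article compares the groups on "mean daily score on the ABS during PTA. This outcome will include all daily ABS assessments throughout the treatment period". No baseline term is attached.

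**Primary model.** Under Analysis of primary and secondary endpoints, the estimand is the "difference in mean daily ABS scores during PTA between olanzapine and control groups", and "a mixed model/multilevel regression framework [72], taking into account duration of PTA, will be employed". PTA duration is the only adjustment named.

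**Two secondary outcomes.** Under Secondary outcomes, item 3 compares "mean ABS score at discharge, controlling for ABS score at treatment commencement". Item 4, mean WPTAS over the treatment period, is compared "controlling for WPTAS score at baseline".

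**Data available.** Under Participant timeline, the day-0 record includes "baseline WPTAS and ABS, demographic information". Table 1 also marks the ABS at baseline.

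**Start of the outcome period.** Under the Treatment heading: "The treatment period will last from day of completion of baseline assessments".

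**Sample size.** 26 per group for a standardised difference of 0.80, with power 0.80 and two-sided alpha 0.05, raised to 29 per group for 10% attrition. The analysis section sets the clinically significant difference at half a pooled SD.

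**The concern.** The baseline value of an outcome is usually a natural covariate for it. Here the same instrument is baseline-adjusted at discharge but not during PTA. WPTAS, which like the primary endpoint is a mean of daily scores over the treatment period, is baseline-adjusted too. The protocol therefore chooses covariates in its own text and gives baseline control to two secondary outcomes without stating it for the primary. The one adjustment it does name, PTA duration, is not a baseline variable and is itself secondary outcome 5, so it cannot stand in for starting agitation.

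At stake is precision. The trial is sized to just reach 80% power at 0.80 SD, and the Discussion calls recruitment its major challenge. The economic evaluation estimates the ABS effect as in the main analysis, so cost per ABS point inherits whatever precision the primary model has.

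There is a smaller related ambiguity. Baseline falls on day 0, the treatment period opens on the day baseline assessments are completed, and the outcome takes in every daily score of that period. The first titration step is a night-time capsule, and the ABS rates the preceding 8 hours. A pre-dose score could therefore be counted as an outcome.

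**Working it through.** **Inputs from the protocol article.** Design effect 0.80 SD; clinically significant difference 0.50 SD; SD 4.1 ABS points; 26 per group; two-sided alpha 0.05; 1:1 allocation; 10% attrition.

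**Input not in the document.** The correlation *r* between baseline ABS and a patient's mean daily ABS during PTA. It is assumed to lie between 0.3 and 0.5. Entry requires a patient to be "judged to be in a state of clinically significant agitation (score > 21) on the Agitated Behaviour Scale", which narrows the baseline range and may lower *r*.

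**Step 1: reproduce the plan's figure.** A two-sample t calculation (noncentral t) at 0.80 SD, power 0.80 and two-sided 0.05 gives 25.52, rounded up to 26 per group. For attrition, 26 / (1 − 0.10) = 28.9, rounded up to 29. Both agree with the protocol. Power at 26 per group is 0.807. The sample size was thus derived without covariate adjustment.

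**Step 2: effect of adjustment.** Adjusting for baseline multiplies the variance of the treatment effect by (1 − *r*²), so the effective standardised difference becomes *d* / √(1 − *r*²).

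| *r* (assumed) | Variance factor | Effective *d* for 0.80 | Power at 0.80 SD | Effective *d* for 0.50 | Power at 0.50 SD |
|---|---|---|---|---|---|
| none | 1.00 | 0.80 | 0.807 | 0.50 | 0.424 |
| 0.3 | 0.91 | 0.80/√0.91 = 0.839 | 0.843 | 0.50/√0.91 = 0.524 | 0.458 |
| 0.5 | 0.75 | 0.80/√0.75 = 0.924 | 0.904 | 0.50/√0.75 = 0.577 | 0.533 |

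In terms of sample size, 26 adjusted patients per group are worth 26/0.91 = 28.6 unadjusted patients per group at *r* = 0.3, and 26/0.75 = 34.7 at *r* = 0.5. With SD 4.1, the approximate 95% half-width is 1.96 × 4.1 × √(2/26) = 2.23 points unadjusted. It becomes 2.13 at *r* = 0.3 and 1.93 at *r* = 0.5.

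**Step 3: cost of the covariate.** One extra parameter at N = 52 inflates the variance by about 1/48. The net factor is (1 − *r*²)(1 + 1/48): 0.929 at *r* = 0.3 and 0.766 at *r* = 0.5. Setting it to 1 gives *r*² = 1/49, so adjustment gains precision once |*r*| exceeds about 0.14. The powers in the table leave out this small cost.

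**Limit of the method.** This is a two-group t approximation on patient means. It does not model repeated daily scores, unequal PTA lengths or the PTA-duration term, so the figures indicate scale rather than the exact power of the planned mixed model.

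**The case against.** **The text may be incomplete rather than wrong.** The protocol promises a detailed statistical analysis plan, which is not shown and may name the covariate. The analysis section describes a framework and does not say that PTA duration is the only term. It also fails to repeat the baseline control that the outcome list gives to discharge ABS and WPTAS, so it is not a full covariate list. This stands in part: one cannot say that baseline ABS is excluded, only that it is not stated. What remains is the contrast inside the outcome list, where two secondary outcomes carry baseline control and the primary does not.

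**A reader might infer bias.** Stratification is not mentioned and groups are small, so chance imbalance in starting agitation may seem to distort the result. With 26 per group, the standard error of the baseline difference is √(2/26) = 0.28 SD. An imbalance of that size would move the unadjusted estimate by about 0.08 SD (*r* = 0.3) to 0.14 SD (*r* = 0.5). Under randomisation the unadjusted estimate is nonetheless unbiased, and its standard error already allows for such imbalance. The documents do not support a claim of bias.

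**A reader might infer that the trial is underpowered because of this.** It is not. The stated 80% power at 0.80 SD was computed without adjustment and holds. The 0.42 at 0.50 SD comes from the choice of design effect, and the covariate raises it only modestly.

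**The correlation is unknown.** This stands. Besides the entry threshold, 8-hour ratings, ABS-guided titration and rescue medication available to both groups could each lower it.

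**The day-0 overlap is a possible reading only.** Also correct. It concerns about one score per patient, in a period that the Background puts at days to months.

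**Conclusion.** The point holds as one of efficiency and consistency. The protocol collects baseline ABS and controls for baseline values in the discharge ABS and mean WPTAS comparisons, but names only PTA duration for the primary comparison. The unadjusted analysis is valid and meets its stated power.

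If *r* is 0.3 to 0.5, the variance falls by about 9% to 25% before the small cost of the extra parameter. Power then rises from 0.81 to 0.84–0.90 at 0.80 SD and from 0.42 to 0.46–0.53 at 0.50 SD. These figures rest on the assumed *r* and on the t approximation. Below about |*r*| = 0.14 nothing would be gained. Whether PTA duration belongs in the model is a separate question, which baseline adjustment does not settle.

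**What to change.** Name pre-dose baseline ABS as a fixed covariate in the primary mixed model, as is already done for ABS at discharge. In the same sentence, state that this pre-dose score serves only as the covariate and is not among the daily scores that form the outcome. Record both in the statistical analysis plan before unblinding, which the protocol places after data cleaning.

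The cost is one degree of freedom and a line or two of text. No new data are needed, and the sample size need not change.

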Agitation may be managed using environmental modifications or pharmacological intervention. However, there is a clear lack of evidence to underpin the use of either of these approaches. A recent systematic review concluded that there exists a paucity of well-designed, adequately powered and controlled studies to support the use of pharmacological intervention for neurobehavioural symptoms during PTA, that clear evidence of efficacy for any pharmacological intervention is lacking and that no pharmacological treatment recommendations could be made [19]. This sentiment is echoed throughout the literature [7, 20–24]. Despite a lack of evidence supporting the efficacy and safety of any pharmacological intervention for agitation during PTA, the use of antipsychotics and anticonvulsants is common [12, 25, 26]. The use of newer atypical antipsychotics is preferred over older typical agents due to findings suggesting more favourable cognitive and motor outcomes associated with their use [27–30]. Such evidence is scant, and questions remain as to whether these agents are effective, and whether their use may have negative side effects such as increasing confusion, prolonging PTA duration and length of hospital stay and ultimately impairing recovery [27–35]. Further, it has been theorised that the administration of antipsychotic agents in TBI patients may impair arousal and cognition, exacerbating confusion, disorientation and drowsiness and in turn deepening PTA [7, 36]. Impairments in cognitive performance following TBI have been reported in animal models administered haloperidol [27–29, 35] and risperidone [27, 28, 35] but not olanzapine [29]. Additionally, antipsychotic administration was associated with prolonged PTA duration in several case series [32, 33, 37]. As improvement in cognition is thought to precede the resolution of agitation [5, 6, 26], the sedating effects of neuroleptics could potentially prolong PTA and serve to heighten or prolong agitation. In the face of such scant evidence, physicians are currently forced to rely on clinical experience, expert advice, low-level evidence and empirical assumptions of how similar conditions are managed in order to make treatment decisions, possibly risking poorer outcomes for patients and exposing staff and caregivers to risk of harm.

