The primary aim of this trial is to evaluate the efficacy of the atypical antipsychotic olanzapine in reducing agitation in patients in PTA following TBI over and above recommended environmental management. We hypothesise that patients who are administered olanzapine will show lower levels of agitation during PTA than those randomised to a placebo control group receiving optimal environmental management. The secondary aims of this research are to determine (1) the safety of olanzapine administration in PTA patients, whether olanzapine treatment: (2) reduces the number of clinically agitated days during PTA, (3) alters level of agitation at hospital discharge, (4) alters level of cognition in PTA, (5) alters PTA duration, (6) alters cognitive performance following PTA emergence, (7) alters length of inpatient hospital stay and (8) alters functional independence at discharge and 3-month follow-up. Finally, this research aims to evaluate the cost-effectiveness of olanzapine administration in PTA patients.

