#### Post-PTA—3 days following emergence from PTA (or 6 months)

Study staff will be informed by ABI ward staff when participants emerge from PTA and treatment will be titrated down as appropriate. Participant consent will be sought as soon as possible following emergence from PTA. Study staff will ask the participant to provide any demographic information unable to be gained from their medical record. Post-PTA measures of weight, BP, HR, WC and blood tests assessing fasting lipids, fasting glucose, HBA1C and creatinine will be conducted. The ABS will be completed daily for 2 weeks following emergence from PTA. Cognitive performance will be measured using the Rey Auditory Verbal Learning Test (RAVLT; [50]) and Oral Symbol Digit Modalities Test (SDMT; [51]). Functional independence will be measured using the Functional Independence Measure (FIM; [52]) and the 12-Item Short Form Health Survey Version 2 (SF-12; [53, 54]). These measures will be completed within 2 weeks of emergence from PTA. If participants remain in PTA at 6 months, treatment will be ceased and measures of weight, BP, HR, WC and blood tests will be administered at this time point. Remaining measures corresponding to the post-PTA time point will be administered upon the participant’s emergence from PTA.

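### The primary ABS mean stops at PTA emergence and its model takes PTA duration into account, so if olanzapine prolongs PTA without calming patients, the comparison tilts in its favour

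*Protocol article*

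**What the plan says.** - **Outcome** (Primary outcome): the groups are compared on "mean daily score on the ABS during PTA", and "This outcome will include all daily ABS assessments throughout the treatment period".
- **End of the window** (Treatment—day 0 until emergence from PTA): "The treatment period will last from day of completion of baseline assessments until the patient is deemed to have emerged from PTA". A 6-month cap applies. The number of days averaged is therefore each patient's own, and it is settled after randomisation.
- **Model** (Analysis of primary and secondary endpoints): "a mixed model/multilevel regression framework [72], taking into account duration of PTA, will be employed". The article does not say how duration is taken into account.
- **Duration as an effect of treatment**: a secondary aim in the Background is whether olanzapine "5) alters PTA duration". The Background also warns that "the sedating effects of neuroleptics could potentially prolong PTA and serve to heighten or prolong agitation".
- **Same window for cognition** (Secondary outcomes): the mean Westmead PTA Scale (WPTAS) score runs "from first day of treatment until emergence from PTA".
- **Data beyond the window** (Post-PTA): "The ABS will be completed daily for 2 weeks following emergence from PTA". These scores are not in the primary outcome.

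**The concern.** Two features make the primary comparison depend on something treatment may change.

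1. **The window.** Agitation tends to settle as patients recover. If a drug delays emergence, it adds late, calmer days to the treated patients' averages and lowers the mean, even when no patient is calmer on any given day.
2. **The model.** If duration is a covariate, the arms are compared at equal observed PTA length. Under prolongation, a treated patient with a 30-day PTA would have emerged sooner untreated, so less severe treated cases are set against more severe placebo cases.

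If agitation instead lasts as long as PTA lasts, stretching both leaves the mean unchanged although patients are agitated for longer. The Abstract says the trial should separate a drug that reduces agitation from one that prolongs agitation and PTA, and the primary test is weak at exactly that. The economic evaluation takes over the same ABS mean.

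**Working it through.** **Inputs from the protocol article.** SD 4.1 for mean daily ABS; effect 0.80 SD; two-sided alpha 0.05; power 0.80; 26 per group before attrition; clinically significant difference 0.5 SD = 0.5 × 4.1 = 2.05 points.

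**The plan's own figure.** A two-sample t test with d = 0.80 has power 0.791 at 25 per group and 0.807 at 26, so 26 is right. 26/(1 − 0.10) = 28.9, so 29 per group. The sample size is not in dispute.

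**Assumptions not in the documents.** Untreated time from randomisation to emergence is lognormal with median 20 days and log-SD 0.6. ABS falls from 26 towards 16 with a time constant of half the PTA length. Daily error SD is 3 and between-patient SD is 4. Olanzapine multiplies PTA length by k = 1.3 or 1.5.

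**Bias from the window alone.** Let agitation follow the untreated course while PTA is stretched k-fold. The expected mean to emergence is 16 + 10(1 − e^(−2k))/(2k).
- k = 1: 16 + 4.32 = 20.32
- k = 1.3: 16 + 3.56 = 19.56, a difference of −0.76
- k = 1.5: 16 + 3.17 = 19.17, a difference of −1.16

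At SD 4.1 and 26 per group, the noncentral t gives the chance of a significant result favouring olanzapine: 8.8% for a bias of −0.7, 9.6% for −0.76, 15.6% for −1.1 and 16.9% for −1.16.

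**Simulation.** 2,000 trials of 26 per group; patient means compared by regression; patient-mean SD about 4.0. Cells give the mean difference (negative favours olanzapine) and the percentage of trials with significant benefit. r is the correlation of agitation level with PTA length.

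| Scenario | k | r | Mean to emergence | Adjusted for log duration | Days 1–14 |
|---|---|---|---|---|---|
| No day's ABS changed | 1.3 | 0 | −0.84, 11% | −0.77, 10% | −0.03, 3% |
| | 1.3 | 0.5 | −0.84, 11% | −1.64, 35% | −0.02, 3% |
| | 1.5 | 0 | −1.15, 16% | −1.07, 14% | 0.07, 2% |
| | 1.5 | 0.5 | −1.16, 17% | −2.43, 64% | 0.06, 2% |
| Agitation tracks PTA | 1.3 | 0 | −0.10, 3% | −0.03, 3% | +0.61, 1% |
| | 1.3 | 0.5 | −0.09, 3% | −0.90, 13% | +0.62, 1% |
| | 1.5 | 0 | −0.01, 3% | 0.07, 2% | +1.05, 0.4% |
| | 1.5 | 0.5 | −0.03, 3% | −1.30, 23% | +1.04, 0.3% |

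With k = 1, every analysis is unbiased at about 3%. Simulations with similar curves put the first scenario at −0.7 to −1.1 points and 8% to 16% unadjusted, 9% to 17% adjusted with r = 0, and 35% to 68% adjusted with r = 0.5. The table agrees within simulation error and choice of curve.

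**Daily mixed model.** Random intercept, first scenario, 600 trials, variance components taken as known. With no time term the bias was −0.75 to −1.26. With day since randomisation but no duration term it was −0.20 to −0.44 for a linear day effect and −0.07 to −0.17 for a logarithmic one, with false benefit in 4% to 8%. With log day and duration it was −0.68 to −2.53.

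**WPTAS.** For linear recovery from 4 to 12, the mean to emergence is 4 + 8 × 5.5/10 = 8.4 over 10 days and 4 + 8 × 30.5/60 = 8.1 over 60 days. It hardly registers a six-fold difference in recovery time. Over a fixed 28 days, scoring 12 after emergence, the means are (10 × 8.4 + 18 × 12)/28 = 10.7 and 4 + 8 × 14.5/60 = 5.9.

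**The case against.** **The phrase about duration is open.** A reader might infer that PTA duration is definitely a covariate. The article does not say so. The wording could refer to unequal numbers of daily scores or to a time term, with detail left to the analysis plan. This stands. Under a day-term reading, the mixed-model check leaves only a small bias.

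**Prolongation is not established.** A reader might infer that olanzapine does prolong PTA. The Background's case series concern antipsychotics generally, and it reports that olanzapine, unlike haloperidol and risperidone, did not impair cognition in animals. The 30% to 50% is an assumption. This stands, but the trial has made the matter a question and should not presume the answer in its primary analysis.

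**The protocol's own mechanism is the second scenario.** It holds that cognition improves before agitation resolves. Without a duration covariate, that scenario gives no false benefit. True, but prolonged agitation then goes unseen in the primary result.

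**Adjustment does not always make things worse.** With r = 0 it makes little difference here. If agitation follows a common calendar curve unrelated to PTA length, adjusting removes the bias.

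**Other outcomes cover this.** A reader might infer that the trial cannot detect prolonged agitation. It can: agitated days, PTA duration and length of stay are secondary outcomes. They do not protect the primary test, and nothing in the article ties its interpretation to them.

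**A fixed window asks a different question.** The hypothesis concerns agitation during PTA. With steps every 3 to 4 days, three escalations take 9 to 12 days, so titration can fill most of 14 days. This is a fair reason not to insist that the window become primary.

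**Conclusion.** The point holds. The averaging window, and on one natural reading a model term, depend on a post-randomisation variable that the trial itself tests as a treatment outcome.

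If olanzapine prolongs PTA by 30% to 50% and changes no day's agitation, the spurious difference without a duration covariate is about −0.7 to −1.1 points. False benefit is then 8% to 16% against a nominal 2.5%. With the covariate it is 9% to 17%, or about 35% to 68% at a correlation of 0.5, where the bias can pass the protocol's 2.05-point threshold. If agitation tracks PTA recovery, the unadjusted mean shows no difference although agitation lasts longer, and the adjusted contrast can favour a harmful drug when agitation correlates with PTA length.

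The bias vanishes if PTA duration is unaffected. The degree of prolongation, the recovery curve and the correlation are all assumptions. The documents do not support saying that the trial will reach a false conclusion, only that its primary analysis is not protected against one.

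**What to change.** 1. **Primary model.** State under Analysis of primary and secondary endpoints that total PTA duration is not a covariate. Handle unequal numbers of daily scores by patient-level random effects and day since randomisation. Adjust only for baseline variables: baseline ABS and days from injury to randomisation.
2. **Fixed-window analysis.** Prespecify daily ABS on days 1 to 14 from randomisation for every patient, in or out of PTA. The two weeks of ABS after emergence cover this for early emergers, apart from withdrawals or scores missed after discharge. Step 1 alone leaves some residual bias; this analysis removes it.
3. **Interpretation.** Require that a superiority claim on the during-PTA mean be read together with the fixed-window result, PTA duration and agitated days. Making the fixed window primary is an option for the sponsor.
4. **WPTAS.** Report a parallel fixed-window analysis, scoring 12 after emergence, as supportive.

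**Cost.** Wording only, with no new assessments. The article reports a recruitment status of 5 and an analysis plan still to be prepared. Three downsides should be acknowledged:
- A 14-day window includes titration and some post-emergence days.
- Its SD is not known to be 4.1. It was 4.3 to 5.0 in the simulation before baseline adjustment, so power needs rechecking if it becomes primary.
- A 21-day window would be incomplete for patients emerging before about day 7, since 7 + 14 = 21.
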